### Surgical Procedure and Study Assessments

#### Phase 1: Screening and eligibility

Potential participants will be identified from sequential patients evaluated at our UCSF Movement Disorders and Neuromodulation Center. After their initial clinic visit and surgical candidacy screening (including careful review of birth and developmental history, prior brain imaging, and other relevant work up), potential study candidates will be identified at a bimonthly group conference devoted to surgical research protocols. A study clinician will then contact eligible subjects and their families to discuss the study and provide the consent form. After an interval of at least 2 weeks to review the consent, potential study subjects and their families will have an in-person visit with study investigators to review the protocol in detail and sign the informed consent (and assent if applicable). All consented study subjects will undergo extensive characterization at their baseline visit including brain MRI, detailed general and neurological examination, standardized videotaped motor exams and QOL rating scales, and formal neuropsychological evaluations.

#### Phase 2: Surgery and open-label titration phase

Study subjects will undergo DBS surgery to be implanted with a totally internalized bidirectional neural interface, Medtronic Percept and Medtronic SenSight electrodes. The stimulation is targeted to the motor dentate nucleus and the cerebellar outflow pathways with the tip of the lead at the proximal (onset) superior cerebellar peduncle, with all contacts except for the most distal one traversing the anterior (motor) dentate nucleus (28). The distal contact is placed 5 mm more posterior to the surface of the brainstem, where the outflow tracts of the cerebellum start to coalesce just anterior to the dentate nucleus. Details on targeting are provided in Cajigas et al. Figure 1e (24), and summarized in a recent review (37) highlighting the accuracy of this targeting method.

The day before surgery, participants are assessed by the anesthesia service. On the day of surgery, electrodes are implanted intracranially and the pulse generator is connected and implanted in the infraclavicular region. Brain imaging confirms the appropriate location of the electrodes. Postoperatively and before discharge, participants are followed closely for wound checks, general and neurological examinations, DBS system integrity checks, and brain signal recordings. They are discharged after 2–3 days with the stimulator off.

There will be a visit ten days after surgery to remove surgical staples and for general and neurological examinations. One month after surgery, the DBS system is turned on and programming starts. Participants and caregivers are given a patient programmer to adjust the participant’s DBS settings as needed and will record any adverse events. The participants are evaluated monthly for four months for additional DBS programming to optimize the stimulation settings.

#### Phase 3: N-of-1 trial phase

Following the open-label phase where the stimulation is optimized, the series of N-of-1 trials will be implemented in the experimental phase (Figure 1). Each trial consists of two one-month periods of either best effective stimulation – determined during the open-label phase – or sham stimulation – ineffective, very low amplitude settings – in alternating order. Patients will be randomly assigned to either sham or effective stimulation as their starting intervention and alternate between the two conditions during the experimental phase. To optimize clinical and research management of participants, a maximum of 2 participants will be studied concurrently but independently. As each trial period ends, another set of 2 participants will be studied, until 5 sets have completed trials. There are 8 possible sequences of 3-cycle combinations of paired arms: AB-AB-AB, AB-AB-BA, AB-BA-AB, AB-BA-BA, and their complements, where A represents effective stimulation and B represents sham stimulation. We will balance the sample by arm and time as follows. To minimize unblinding, concurrent participants will not be assigned to the same sequence: within each set, one of 8 sequences will be randomly assigned to the first participant and one of the remaining 7 sequences to the second participant. Across sets, balance in the starting arm will be maintained by restricting the sequences as needed, so that 5 of 10 participants begin their trial on the intervention arm and 5 on the placebo arm.

Patients and caregivers will be blinded to treatment assignment after the open-label phase. To ensure appropriate blinding of procedures from the investigator’s side, there will be a designated DBS programming clinician who will implement the treatment (effective/sham stimulation) independent from a rating investigator clinician who will assess the outcome measures. The participants will wear a hat/cap to conceal time from surgery for videotaped motor assessments.

#### Phase 4: Subsequent follow-up

After the three N-of-1 blocks, the last clinic visit of the study will include repeated neuropsychological testing, QOL and pain questionnaires, videotaped motor assessments, brain recordings, and a second brain MRI. After the conclusion of the study, and for five years following DBS surgery, participants will be invited to return yearly for a research visit for DBS checks and detailed assessments of neurological and behavioral function.

### Participant’s withdrawal

Participants will have the right to withdraw from the trial either fully or partially at any point in time. Follow-up care and testing will be determined before withdrawal to ensure participation is stopped safely. Any data we have already collected from the participant will remain part of the study records. If stimulation is deemed ineffective, surgical removal of the device will be offered to the participant.

### Data management and confidentiality

To ensure confidentiality, participants will be given a research identification number and all data related to any particular participant will be collected and stored using such identification number. Representatives from the National Institutes of Health (NIH), University of California, U.S. FDA, and Office of Human Research Protections (OHRP) may review the data for monitoring or managing study conduct. The study dataset will contain range checks and data validation to ensure data accuracy. Electronic data collection forms will be utilized for each study visit using REDCap, a secure, encrypted, UCSF-sanctioned browser-based metadata-driven electronic data capture system and will be designed to incorporate NINDS Common Data Elements recommendations. The Data Safety Monitoring Board (DSMB) for this study is a panel composed of three external members who will review the study data on a regular basis. Treatment-related adverse events noted by any study personnel classified as definitely, probably, or possibly related to study procedures and as either serious or unexpected, will be reported to the DSMB, IRB, FDA, NIH, and manufacturer.

### Statistical Analysis

The primary analysis will use the N-of-1 trials to obtain individual and population-level estimates of the efficacy of cerebellar DBS in ameliorating movement disorder symptoms and in improving QOL for children and young adults with DCP. We will use an intention-to-treat analysis. We anticipate that, within each participant, within-arm CPCHILD and MD-CRS 4–18-R scores measuring the effects of cerebellar stimulation will be relatively stable over time, with slopes approximately parallel with some possible carryover from the effective to sham stimulation arm, based on our prior experience with cerebellar DBS(24). Based on weekly assessments, each participant will contribute 4 values per arm per block. Within each block, we will treat the participant’s arm-specific values as simultaneous replicates and attribute them to the midpoint of the relevant follow-up interval.

To accommodate alternatives to Gaussian distributions of the measured outcomes, we will analyze them using a generalized linear mixed model (GLMM), with treatment arm, and follow-up time as fixed effects and the subject as a random effect. With 3 blocks per arm, an arm-by-time interaction is unlikely to be needed but will be evaluated in a sensitivity analysis; we will also consider a simplification of the model that substitutes blocks for time. Output of the model will include estimates of the participant-specific mean (95% confidence interval) difference between arms, as well as the overall mean difference (95% confidence interval) between arms and overall plot. An interim analysis of the success of cerebellar stimulation will be performed after the first set of 2 subjects is studied.

The N-of-1 trial design is particularly useful when treatment effects exhibit variability between individuals (38), as is the case for DBS for complex movement disorders in DCP(10). N-of-1 designs provide the most rigorous evidence for treatment decisions at the individual level. In addition, when outcomes are aggregated from several patients, N-of-1 trials can yield treatment effect estimates applicable to the broader population, and close to the level of evidence of randomized controlled trials (39). While not previously used in DBS for dystonia, the N-of-1 design was found to be useful for assessing DBS efficacy in neuropathic pain (40), and it has been more recently recommended for uncommon movement disorders (41).

An assumption for N-of-1 trials is that the treatment to be assessed should have relatively rapid onset and washout, with limited carryover effects. While the beneficial effects of DBS in dystonia following pallidal stimulation may manifest after a delay, non-invasive cerebellar transcranial magnetic stimulation (TMS) and transcranial direct current stimulation (tDCS), and cerebellar DBS appears to have a fast onset and quick wash-out of benefit(24). If significant delayed-onset and carry-over are observed (during interim analyses), the blinded assessments at the 12-month visit (compared to pre-stimulation baseline) will be used as an endpoint for efficacy. If participants do not tolerate sham or effective stimulation due to resurfacing of dystonia/choreoathetosis, spasticity, and/or pain, we will shorten each block duration by two-to-three weeks. If this is not tolerated, we will continue effective (or sham) stimulation and analyze data for that participant both as intention-to-treat and on an ‘as treated’ basis. The percentage of participants who successfully identify their stimulation settings (effective vs. sham) and are unable to tolerate sham or effective settings will be considered a surrogate secondary endpoint for preliminary effectiveness. In that instance, the effects of the open-label intervention on the blinded video motor ratings and QOL at five months (before the randomized phase) and at 12 months, will be compared to the preoperative baseline.

DBS is considered a minimally invasive surgical option for patients with movement disorders, as it is reversible, adjustable, and has a well-tolerated safety profile. However, given the novelty of the brain target, it is considered an experimental therapy. The risks of intracranial hemorrhage from DBS electrode placement in cerebellar targets are expected to be similar to that for other brain targets (0.2–1.8%)(42). However, the consequences of intracranial hemorrhages in the posterior fossa are greater for a given size of hematoma, and in the event of bleeding, carry a higher risk for the need for surgical decompression. Protection from these surgical risks includes routine neurosurgical practices such as preoperative prophylactic antibiotics, strict intra-operative control of blood pressure, and preoperative checks of coagulation factors. Intraoperative computed tomography CT will be used to confirm the intended placement. The risk of brainstem dysfunction post-operatively is reduced by not advancing the lead all the way to the edge of the brainstem. The youngest participant’s age will be 7 at time of surgery. At this age, no additional growth of cranial structures is expected to be enough to pose a threat to lead placement. Lead migrations in children 7 and older with cerebral palsy are not any more common than in adult populations(43). Additionally, any potential lead migrations would be expected to be posteriorly, away from the brainstem, posing less risk to brainstem structures.

Since cerebellar stimulation is a relatively novel target, cerebellar stimulation-related side effects are unknown. Some potential adverse effects during cerebellar stimulation may include stimulation-induced dysarthria, hypotonia, and ataxia. To prevent these risks, a wide range of symptoms is consistently monitored by movement disorder specialists.

Brain recordings may also shorten the lifespan of the implanted battery, requiring an earlier-than-expected replacement. Our data collection will be limited to one- hour maximum per session, which would only reduce the implantable pulse generator’s longevity by a few days (44).

Additionally, the use of DBS in children has its own bioethical, social, and legal considerations, and evidence from the adult DBS literature may not be readily translatable to children (45). This study will enroll vulnerable populations, including children seven years and older and individuals who may have intellectual disabilities. The rationale for involving these populations is the need for better therapies to improve movement disorders, tone, and QOL for them. Only those patients refractory to prior treatments and considered adequate candidates for DBS are recruited. First-hand evidence in these vulnerable groups is needed, as children and young adults with dyskinetic CP are rarely included in trials. Their exclusion may deprive them from the benefits of research and expose them to additional risks if interventions are later used on them without adequate data (46).

This trial has primary objectives to assess the feasibility and safety of cerebellar DBS in addressing movement and tone disorders in children and young adults with DCP. Clinical outcomes include average total CPCHILD score and average total MD-CRS 4–18-R scores, and key secondary outcome measures include other health-related QOL scores, other motor and spasticity ratings, and exploratory automatic video kinematic analyses. The information and outcomes gathered from this study will be pivotal for establishing the principles and generating a robust methodological framework to develop DBS therapy in DCP.

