**Methods::**

Ten children and young adults with DCP and disabling movement disorders with or without spasticity will undergo bilateral DBS in the dorsal dentate nucleus, with the most distal contact ending in the superior cerebellar peduncle. We will implant Medtronic Percept, a bidirectional neurostimulator that can sense and store brain activity and deliver DBS therapy. The efficacy of cerebellar DBS in improving quality of life and motor outcomes will be tested by a series of N-of-1 clinical trials. Each N-of-1 trial will consist of three blocks, each consisting of one month of effective stimulation and one month of sham stimulation in a random order with weekly motor and quality of life scales as primary and secondary outcomes. In addition, we will characterize abnormal patterns of cerebellar oscillatory activity measured by local field potentials from the intracranial electrodes related to clinical assessments and wearable monitors. Pre- and 12-month postoperative volumetric structural and functional MRI and diffusion tensor imaging will be used to identify candidate imaging markers of baseline disease severity and response to DBS.

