#### Sample Size

The power calculation (35) is based on the more variable CPCHILD score. Standardized CPCHILD scores, which range from 0 (best) to 100 (worst), will be calculated for each of the scale’s seven domains and the total survey (calculated by dividing raw scores by the maximum item score, multiplied by 100). We chose a 10-point difference as a clinically relevant difference between sham and effective stimulation (13). Assuming normally distributed differences and treatment-by-patient interaction standard deviation of 12.6 based on previously published data (36), relatively stable disease and minimal carry-over of effects, and a type I error rate of 0.05 (two-sided), a chosen sample size of n=10 would have over 80% power to detect clinically relevant differences.

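### Treating a month's four weekly scores as replicates, with subject as the only named random effect, makes standard errors too small if scores within a month are correlated

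*Protocol article*

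**What the plan says.** The abstract describes "three blocks, each consisting of one month of effective stimulation and one month of sham stimulation in a random order". That makes six randomised treatment months per participant and 60 over ten participants.

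The Statistical Analysis section then moves to the weekly level: "Based on weekly assessments, each participant will contribute 4 values per arm per block". It treats those "arm-specific values as simultaneous replicates and attribute them to the midpoint of the relevant follow-up interval". The model is a GLMM with arm and follow-up time as fixed effects, and the subject is the one random effect named. An arm-by-time interaction is reserved for a sensitivity analysis, and replacing time by block is mentioned as a simplification. The promised output is an arm difference with a 95% interval for each participant, and one overall.

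No term for the participant's treatment month and no serial correlation is named. The Sample Size section sets a two-sided 5% level.

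**The concern.** A subject intercept absorbs only what stays constant across all six months. It does not absorb what one participant's four scores share within a single month, such as an intercurrent illness or a change in circumstances at home. That shared deviation coincides with whichever arm was assigned to the month, so it belongs in the standard error of the arm difference. More weekly readings within the month do not average it away.

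Given subject, the model as named treats the 240 weekly values as independent. Neither variant of the model repairs this. An arm-by-time term is a fixed effect. A block contains one month of each arm, and a fixed block effect is common to all participants.

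The intervals for both primary outcomes are at stake, overall and for each participant. The participant-level intervals matter most, because the article presents N-of-1 evidence as a basis for individual decisions.

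**Working it through.** **Inputs from the article.** 10 participants, 3 blocks, 2 months per block, 4 weekly values per month, two-sided 5% level. Values per arm: 3 × 4 = 12 per participant, 120 in all. Months per arm: 3 per participant, 30 in all.

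**Assumed input.** The correlation r among a participant's weekly scores within a month, beyond the subject effect. The article does not give it, so a range is shown.

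**Plan's own figure.** The only error rate stated is the nominal 5%. At r = 0 the model as named reproduces it (simulated 0.045). The power figure concerns another quantity and is not used here.

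**Standard error.** With within-subject variance σ², the mean of four weekly scores has variance σ²[r + (1 − r)/4] = (σ²/4)(1 + 3r). The model as named uses σ²/4. The standard error is therefore too small by a factor of about √(1 + 3r), and the null rejection rate is about 2[1 − Φ(1.96/√(1 + 3r))].

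Example with σ = 10 and r = 0.5:
- Weekly values as replicates: 10 × √(2/120) = 1.29.
- Months as units: 10 × √(0.625 × 2/30) = 2.04.
- Simulation gave 1.24 and 2.06.

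**Simulation.** No effect in anyone; sequences drawn by the article's allocation rules; subject intercept, arm and linear time; 6,000 trials per setting.

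| r | √(1+3r) | Formula | Model as named | One participant, weekly values | 60 month means |
|---|---|---|---|---|---|
| 0 | 1.00 | 0.050 | 0.045 | 0.053 | 0.045 |
| 0.1 | 1.14 | 0.086 | 0.090 | 0.092 | 0.056 |
| 0.3 | 1.38 | 0.155 | 0.168 | 0.163 | 0.048 |
| 0.5 | 1.58 | 0.215 | 0.229 | 0.234 | 0.047 |

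A separate simulation of 4,000 trials gave 0.162 at r = 0.3 and 0.240 at r = 0.5. At r = 0.3, the 12 values per arm are worth 12/1.9 = 6.3.

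**Serial correlation instead of a shared month effect.** With weekly AR(1) correlation of 0.2, 0.5, 0.7 and 0.9, the model as named rejects in 0.089, 0.148, 0.166 and 0.142 of null trials.

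**With a random arm-by-subject slope (overall test).** For r from 0.1 to 0.7, the Wald z test rejects in 0.059 to 0.083. A t test on 9 degrees of freedom rejects in 0.031 to 0.050.

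**With that slope (participant intervals).** Take σ = 10 and r = 0.3 (both assumed), and let true effects vary with the SD of 12.6 from the Sample Size section (variance 158.76).
- Error variance of one participant's difference: the model uses 2 × 100/12 = 16.67; the true value is 16.67 × 1.9 = 31.67.
- The excess of 15.00 is read as slope variance: 158.76 + 15.00 = 173.76.
- Weight on the participant's own data: 173.76/(173.76 + 16.67) = 0.912.
- SD claimed by the model: √(0.912 × 16.67) = 3.90.
- Actual root mean square error: √(0.088² × 158.76 + 0.912² × 31.67) = 5.25.
- Ratio 1.35, so a nominal 95% interval misses in about 2[1 − Φ(1.96/1.35)] ≈ 15% of cases.

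**The case against.** **The model as named cannot deliver its own output.** A subject intercept alone gives every participant the same arm difference. Promising participant-specific differences therefore implies an arm-by-subject term that the article does not spell out. This stands, and it means the 9–24% range should not be read as the unconditional error rate of the overall test. It does not rescue the participant intervals: a slope is shared by all of a participant's months, so it cannot separate month-level noise from a real individual effect.

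**The article never says the values are independent, and covariance detail usually sits in the full plan.** The first part is true: independence given subject is what the named model implies, not a stated claim. But the article gives a positive rule (replicates at a common time point, subject as random effect), and following it as written produces the problem.

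**The correlation is unknown and may be low.** This stands for the size. The expectation of fairly stable scores supports no particular value. At exactly zero there is no inflation.

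**Two further inferences go too far.** A reader might conclude that participants will be wrongly declared responders, but the article contains no responder rule, only estimates and intervals. A reader might also blame the constant caregiver, rater or stimulation setting. Anything constant across a participant's months is absorbed by the subject effect, and the setting is the arm itself. Only what varies from month to month counts.

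**Conclusion.** The concern holds in conditional form. As written, the analysis takes the week as its unit while the month is randomised, so standard errors are too small for any positive within-month correlation. Under the model as named, null rejection is about 5%, 9%, 16% and 24% at assumed correlations of 0, 0.1, 0.3 and 0.5. With a random arm-by-subject slope, the overall test is nearly repaired (about 6–8% by Wald z, about 5% or less with t on 9 degrees of freedom), and the weight of the point shifts to the participant-specific intervals. The direction is certain for positive correlation. The size rests on a correlation the document does not supply, on Gaussian outcomes and, for the slope calculation, on the assumed within-subject SD of 10.

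**What to change.** Before unblinding, choose one of these and state it:

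- Add a random effect for the participant's treatment month (subject-by-block-by-arm) to the model, with small-sample degrees of freedom.
- Analyse the 60 month means, also with small-sample degrees of freedom. This restores a null rejection rate of 0.045 to 0.056 under a shared month effect.

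State as well whether the model includes a random arm-by-subject slope. Base each participant's interval on the month-level variance pooled across participants.

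**Cost.** One more variance component and wider intervals; no new data. Building an interval only on a participant's own three block differences would cost far more: with 2 degrees of freedom the t multiplier is 4.30 against 2.07 on 22, and at a correlation of 0.3 the interval becomes (4.30/2.07) × 1.38 ≈ 2.9 times as wide. The pooled version is preferable.

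**Remaining limit.** Under strong serial correlation across months, the month-mean analysis becomes conservative (0.022 at weekly AR(1) 0.7, 0.005 at 0.9). For the overall effect, a t test on one difference per participant stays at 0.043 to 0.055 under AR(1) and is a useful sensitivity analysis.

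### As worded, the primary mixed model has no subject-by-arm effect, so it cannot give the promised participant-specific differences and would make the overall confidence interval too narrow

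*Protocol article*

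**What the plan says.** The Statistical Analysis section of the protocol article sets out a generalized linear mixed model "with treatment arm, and follow-up time as fixed effects and the subject as a random effect". It considers two variations: an arm-by-time interaction as a sensitivity analysis, and blocks in place of time. Neither lets the arm effect differ between participants.

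The same paragraph states two outputs. The first is individual: "Output of the model will include estimates of the participant-specific mean (95% confidence interval) difference between arms". The second is at population level: "as well as the overall mean difference (95% confidence interval) between arms and overall plot". On the data, "each participant will contribute 4 values per arm per block", and these weekly values are handled as replicates within arm and block.

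Two other statements show that the authors expect effects to differ between participants. The Statistical Analysis section calls the N-of-1 design "particularly useful when treatment effects exhibit variability between individuals" and says that this is the case here. The Sample Size section bases the power on a "treatment-by-patient interaction standard deviation of 12.6 based on previously published data".

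**The concern.** Read as written, subject is the only random effect and arm is a common fixed effect. That is a random-intercept model: participants may differ in their general level, but not in how much stimulation changes them. Both promised outputs are affected.

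- **Individual estimates.** The model has one arm difference, shared by all. Participant-specific differences, which the section names as an aim of the primary analysis, are not among its parameters.
- **Population estimate.** To speak about patients beyond these ten, the standard error must include the spread of effects between patients. The random-intercept model pushes that spread into the residual and divides it over 240 values instead of 10 participants.

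The practical stake is an overall result that looks much more certain than it is. At an assumed weekly SD of 10 (see the working), an observed difference of 5 points would exclude zero with the random-intercept half-width of about 3.0, but not with the correct half-width of about 9.5.

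**Working it through.** **Inputs.** From the Sample Size section: n = 10, a relevant difference of 10 CPCHILD points, two-sided alpha 0.05, and interaction SD τ = 12.6. From the design: 3 blocks with 4 values per arm per block, so m = 3 × 4 = 12 values per arm per participant and N = 2 × 12 × 10 = 240. The within-patient weekly SD, s, is not given. I assume a range of 0 to 20. The formulas take an identity link, normal outcomes and independent weekly errors.

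**1. The plan's own figure.** The plan states that "a type I error rate of 0.05 (two-sided), a chosen sample size of n=10 would have over 80% power". With τ as the SD of ten participant differences, SE = 12.6/√10 = 3.98 and 10/3.98 = 2.51. Power is 61% by noncentral t (9 df), or Φ(2.51 − 1.96) = 71% by normal approximation. The stated power is not reproduced, and any within-patient error lowers it further. Values near or above 80% need readings that the text does not state:

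- one-sided normal approximation: 80.6%;
- 12.6 as a within-patient SD over 3 cycles (SD of the difference 12.6 × √(2/3) = 10.29): 78% by t, 87% by normal;
- 12.6 as the SD of a per-cycle difference (12.6/√3 = 7.27): 97%.

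This is a separate issue. It matters here only because it leaves some doubt about what 12.6 measures.

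**2. What the model can output.** With a random intercept, the linear predictor for participant i is μ + uᵢ + β·arm + γ·time. Effective minus sham is β for every i. Only an added term bᵢ·arm gives participant i a difference of their own, β + bᵢ.

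**3. Standard errors of the overall difference.**

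- Correct: SE_c = √(τ²/10 + 2s²/120), with t on 9 df (multiplier 2.262).
- Random intercept: the residual absorbs the interaction, so MSE = s² + 9 × 6 × τ²/228, where 228 = 240 − 10 − 2. Then SE_m = √(4 × MSE/240), with multiplier 1.96.
- False-positive rate when the average effect is zero but individual effects vary: 2[1 − Φ(1.96 × SE_m/SE_c)].

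At s = 10: SE_c = √(15.88 + 1.67) = 4.19. MSE = 100 + 37.6 = 137.6, so SE_m = √2.293 = 1.51. The half-widths are 2.262 × 4.19 = 9.5 and 1.96 × 1.51 = 3.0, a ratio of 0.31.

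| Weekly SD s (assumed) | SE_c | SE_m | CI width ratio | False-positive rate |
|---|---|---|---|---|
| 0 | 3.98 | 0.79 | 0.17 | 70% |
| 5 | 4.04 | 1.02 | 0.22 | 62% |
| 10 | 4.19 | 1.51 | 0.31 | 48% |
| 15 | 4.43 | 2.09 | 0.41 | 36% |
| 20 | 4.75 | 2.70 | 0.49 | 27% |

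Part of the ratio is the choice of z over t (1.96/2.262 = 0.87). The ratio of standard errors alone runs from 0.20 to 0.57.

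**4. Sensitivity.**

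- τ = 6, s = 10: SE_c = 2.30, SE_m = 1.35, CI ratio 0.51, false-positive rate 25%.
- Each arm-block reduced to one mean (60 values), τ = 12.6: CI ratio about 0.38 to 0.57 over the same range of s.
- τ = 0: the two standard errors are equal and the problem disappears.

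**5. Simulation.** Random-intercept models fitted to simulated trials (150 runs per setting) gave median CI ratios of 0.22, 0.33 and 0.43 at s = 5, 10 and 15, and rejection rates of 62%, 49% and 29%. A larger simulation (4,000 trials per setting) of an equivalent within-subject regression gave 62%, 47% and 37%. Both agree with the formulas within simulation error.

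**The case against.** The strongest reply is that naming the subject as a random effect does not say intercept only. Because the paragraph promises participant-specific differences, a random treatment effect may be meant in shorthand. An article may also leave the full random-effects structure to the analysis plan. This has some force: a reader might infer that the trial will certainly fit a random-intercept model and produce no individual estimates, and the text does not establish that. But the article goes beyond silence. It lists the terms, considers a different interaction, and promises an output that the listed terms do not give. The degrees-of-freedom method alone would be no finding.

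A reader might also infer that the interval will be about a third of its correct width. The documents do not support a fixed figure. A third needs a weekly SD of about 10 to 11, which the protocol does not state, and needs 12.6 to be the SD of participant-level differences, which step 1 leaves in some doubt. A smaller interaction usually means a milder effect.

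Two further points are fair but limited. With a non-identity link, a random intercept gives response-scale differences that vary with baseline, but that is not variation in the treatment effect. And the false-positive rates apply to a zero average effect with varying individual effects, not to a null of no effect in anyone. Since the section seeks population-level estimates and expects effects to vary, the first null is the relevant one.

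**Conclusion.** The concern holds in conditional form. If the model is fitted as worded, it cannot give the promised participant-specific differences, and its overall interval omits the between-participant variation on which the sample size rests. The first part needs no numerical assumption. Nor does the direction of the second, provided effects vary between participants.

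The size does rest on assumptions: 12.6 as the SD of participant-level CPCHILD differences, 240 independent weekly values, and an assumed weekly SD. For a weekly SD of 0 to 20 the interval is about 0.17 to 0.49 of the correct width, and about 0.5 at interaction SD 6 with weekly SD 10. False-positive rates are roughly 36% to 62% for weekly SD 15 down to 5. The model is meant for both primary outcomes, but the documents give no figure from which to size the effect on the motor scale.

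**What to change.** State the primary model as: fixed effects for arm and time; a random subject intercept; and a random subject-by-arm (treatment) effect. Use small-sample degrees of freedom, such as Kenward-Roger or Satterthwaite, for the overall difference; these will be about 9 with ten participants. Report the participant-specific differences and their intervals from this model. They will be shrunken towards the overall mean, so each participant's own unshrunken paired difference could be shown beside them. If a random treatment effect was intended all along, the change is one clarifying clause.

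The edit is about one line and needs no new data. The cost is a wider overall interval: at the assumed weekly SD of 10, a half-width of about 9.5 points instead of 3.0, against the plan's relevant difference of 10.
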